#### Secondary

2. Changes in general cognition in patients taking donepezil assessed using MMSE score from baseline to 12 weeks.3. Changes in clinical severity in patients taking donepezil assessed using CDR score from baseline to 12 weeks.4. Changes in cognitive function in patients taking donepezil assessed using CDR score from baseline to 12 weeks.5. Determination of changes in ADL in patients taking donepezil assessed using S-IADL score from baseline to 12 weeks.6. Changes in visuospatial dysfunction in patients taking donepezil assessed using VOSP score from baseline to 12 weeks.7. The assessment of digital pen data involves a simplified RCFT and digital CDT in patients taking donepezil. Digital pen data can serve as a biomarker to detect subtle changes in visuospatial function.8. The assessment of eye-tracking metrics involves a digital CDT in patients taking donepezil. Eye-tracking metrics can serve as a biomarker to detect subtle changes in visuospatial function.

### Participant timeline {13}

The participant timeline and visit schedules are illustrated in Figs. 1 and 2.

### Sample size {14}

The sample size was calculated to test differences in the primary outcome between the donepezil and control groups based on the standardized effect size commonly used in clinical studies on cognitive impairment [16, 17]. The standardized effect of donepezil on cognitive tests scores was reported as medium to large size (0.3 ~ 1.9) [18–21]. A recent study showed that fixation frequency had a large effect size (0.8) for the difference between apathetic and non-apathetic AD [22]. This suggests that eye-tracking metrics, such as fixation, might be more sensitive than cognitive scores; therefore, a large standardized effect can be expected in this trial.

A sample size of 34 patients per group achieved 90% power to detect a standardized effect size of 0.8 with a significance level of 0.05, using a two-sided two-sample *t*-test. The standardized effect size of this study was set as the lower bound of the large effect size range (> 0.8) using a conservative approach. Assuming an attrition rate of 12%, a total sample size of 78 (39 patients per group) should be enrolled. The sample size was calculated using PASS 22.0.2.

### Recruitment {15}

Participants will be recruited from among those who visited the Memory Disorder Clinic in Jeonbuk National University Hospital.

## Assignment of interventions: allocation

### Sequence generation {16a}

COG-EYE is a randomized, open-label, parallel design trial; the participants will be randomized 1:1 for donepezil: control. We will perform the allocation using a block randomization method of size six. Randomized allocation will be carried out sequentially, and once assigned, the randomization code cannot be reassigned to another participant, even if the participant withdraws consent. The investigators and participants will not be blinded to the allocation after assignment. To minimize bias in the open-label study, we will set the primary outcome as eye-tracking metrics rather than clinical rating scores.

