## Methods: participants, interventions, and outcomes

### Study setting {9}

This study will be conducted in a single center, Biomedical Research Institute, Jeonbuk National University Hospital.

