### Concealment mechanism {16b}

First, the allocation code will be generated by the Biomedical Research Institute of Jeonbuk National University Hospital. Second, participants will be assigned to each arm according to sequential numbers after general screening. Because this is an open-label study, participants, caregivers, principal investigator, and all staff will not be blinded after allocation. Only the participants allocated to the donepezil group will receive investigational medicinal product (IMP).

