### Implementation {16c}

The allocation code will be generated by the Biomedical Research Institute of Jeonbuk National University Hospital. The research staff and the principal investigator will enroll participants, and recruited participants will be given an identification number sequentially. Randomized allocation will then be performed after baseline screening, according to the sequential identification number.

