## Assignment of interventions: blinding

### Who will be blinded {17a}

COG-EYE is an open-label trial; thus, participants, caregivers, principal investigator, and staff will not be blinded.

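### A single fixed block size of six in an open-label, single-centre trial makes about a quarter of allocations deducible by the staff who enrol

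*Protocol article*

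**What the plan says.** All references are to the protocol article.

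- **Sequence generation {16a}:** "the participants will be randomized 1:1 for donepezil: control" and "We will perform the allocation using a block randomization method of size six". No other block size is named.
- **Study setting {9}:** "This study will be conducted in a single center". No stratification factor is stated, so the text implies one running sequence.
- **Concealment mechanism {16b}:** the hospital's Biomedical Research Institute generates the code, "participants will be assigned to each arm according to sequential numbers after general screening", and "participants, caregivers, principal investigator, and all staff will not be blinded after allocation". Only the donepezil arm receives study drug.
- **Implementation {16c}:** "The research staff and the principal investigator will enroll participants, and recruited participants will be given an identification number sequentially". Allocation follows that number after baseline screening.
- **Who will be blinded {17a}:** "participants, caregivers, principal investigator, and staff will not be blinded".
- **Eligibility criteria {10}:** exclusion 17 rests on the investigator's judgement.
- **Trial status:** recruitment runs from July 2021 to December 2023. The article was published on 27 September 2022.

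The one measure offered against open-label bias, in Sequence generation {16a}, is the choice of an eye-tracking primary outcome.

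**The concern.** Every block of six holds exactly three allocations to each arm. Once three of one arm have been used, the rest of that block is settled. In a blinded trial, or one with many centres, the people enrolling could not usually see this. Here the same unblinded people enrol participants and see all earlier assignments in what appears to be a single sequence.

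Keeping the list away from the clinic hides the next code on paper. It does not prevent the code from being worked out from the visible past allocations and a known block size.

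At stake is the comparability of the two groups at entry. Someone who knows the next arm can, without intending to, hurry, delay or decline a particular participant. The eye-tracking outcome protects against biased assessment, not against this. The baseline-adjusted analysis in Statistical methods {20a} deals with imbalance in the measured baseline value of each outcome, but not with unmeasured differences.

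**Working it through.** **Inputs.** Block size 6 and ratio 1:1 (Sequence generation {16a}); total 78, 39 per group (Sample size {14}); one sequence (inferred from Study setting {9} and the absence of any stated stratification).

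**The plan's own figure.** With 34 per group, a standardized effect of 0.8 and two-sided 0.05, noncentral-t power is 0.9015 (33 per group gives 0.8926). Then 34 / (1 − 0.12) = 38.6, rounded up to 39 per group, 78 in total. The sample size reproduces and this point does not affect it. 78 / 6 = 13 complete blocks.

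**Allocations known with certainty.** A 3:3 block has C(6,3) = 20 equally likely orders.

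- 4th known: the first three are all one arm. 2/20 = 0.10.
- 5th known: the last two are the same arm. 2 × C(4,1)/20 = 8/20 = 0.40.
- 6th known: always. 1.00.

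The sum is 0.10 + 0.40 + 1.00 = 1.5 per block. 1.5/6 = 25%, and 13 × 1.5 = 19.5 of 78.

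**Only future allocations can be protected.** July 2021 to December 2023 is 30 months, and publication fell about 15 months in. Assuming even accrual (an assumption, since the article gives no accrual figures), about 39 participants remained at publication, and 0.25 × 39 = 9.75 certain allocations.

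**Guessing the arm that is behind so far.** In a balanced block of 2m, this rule is right m times plus one half for each tie met before the block ends. For m = 3, ties occur at the start (probability 1), after two allocations (C(2,1) × C(4,2)/20 = 0.6) and after four (0.6). Expected correct guesses are 3 + 0.5 × (1 + 0.6 + 0.6) = 4.1 of 6, or 68.3%. Over 78 that is 53.3, against 39 by chance.

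**Effect of varying the sizes.** Simulation of 2,000 lists of 78, where the person guessing knows the set of sizes but not their order:

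| Block sizes | Known with certainty | Guess correct |
|---|---|---|
| 6 only | 25.0% | 68.3% |
| 4, 6 | 5.5% | 69.2% |
| 4, 6, 8 | 2.3% | 67.9% |
| 6, 8, 10 | 1.6% | 66.1% |

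With 4, 6 and 8, certain allocations fall from 19.5 to about 0.023 × 78 = 1.8 over a full list. The guess rate hardly moves.

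**The case against.** Fixed-size permuted blocks are a legitimate method, and nothing here is an internal contradiction. Most entry criteria are objective: amyloid PET, MRI, MMSE, visual acuity, education and prior drug use. This narrows the room for steering, although exclusion 17 and the timing of entry remain. The article does not say whether enrolling staff knew the block size before it was published, so 19.5 of 78 is an upper bound. How codes are released may be described in the full protocol, which is not shown, so its absence from the article is not a fault. All of this stands and limits the size of the point. The deduction itself remains, because it needs only the published block size and open past allocations.

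Three stronger readings are tempting, but the documents do not support them.

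- **The 68% guess rate is a harm of the fixed, published size.** It is not. The rule needs no knowledge of block size and works about as well with sizes of 4, 6 and 8. Only the 25% certainty figure bears on this design choice.
- **Screen failures use up codes and lose the 39/39 balance.** Implementation {16c} is loose about when the identification number is issued. However, it gives numbers to recruited participants, and Concealment mechanism {16b} and Intervention description {11a} place allocation after screening. Nothing says that a screen failure consumes a code.
- **Selection bias has occurred, or nothing in the analysis could help.** The article shows a risk only, and baseline adjustment would deal with part of any measured imbalance.

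**Conclusion.** The point holds as a design weakness worth correcting. As written, the plan lets an enroller who knows the block size and follows the tally deduce 25% of allocations on average, up to 19.5 of 78. About 9 to 10 of these could still be protected if the change came at publication and accrual was even. The figures assume one unstratified sequence, staff who know the size, and someone keeping count. All three are plausible at a single open-label site with the size in print, but none is demonstrated. How far any steering could shift the eye-tracking outcome cannot be estimated from the article. Sample size and power are unaffected, and the weakness does not by itself invalidate the trial.

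**What to change.** For participants not yet randomised, amend Sequence generation {16a} and Concealment mechanism {16b} so that:

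1. the remaining list uses randomly varying block sizes, for example 4, 6 and 8;
2. the sizes and their order are withheld from everyone who enrols until recruitment closes;
3. each allocation is released only after eligibility has been confirmed and recorded.

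Step 1 removes most of the certainty, to about 2% even if the set of sizes becomes known. It does not remove the advantage of guessing the arm that is behind, so step 3 matters as well: once eligibility is recorded, a guess has less room to influence who enters.

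The cost is regenerating the remaining list, one amendment and a possible final imbalance of a few participants (at most 4 from an unfinished last block of eight). The total of 78 does not change.

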### Concealment mechanism {16b}

First, the allocation code will be generated by the Biomedical Research Institute of Jeonbuk National University Hospital. Second, participants will be assigned to each arm according to sequential numbers after general screening. Because this is an open-label study, participants, caregivers, principal investigator, and all staff will not be blinded after allocation. Only the participants allocated to the donepezil group will receive investigational medicinal product (IMP).

### Implementation {16c}

The allocation code will be generated by the Biomedical Research Institute of Jeonbuk National University Hospital. The research staff and the principal investigator will enroll participants, and recruited participants will be given an identification number sequentially. Randomized allocation will then be performed after baseline screening, according to the sequential identification number.

## Assignment of interventions: blinding

### Who will be blinded {17a}

COG-EYE is an open-label trial; thus, participants, caregivers, principal investigator, and staff will not be blinded.

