**Fig. 2 Fig2:**
[figure not shown]
COG-EYE schedule of enrolment, interventions, and assessments**.** CDR, Clinical Dementia Rating; ECG, echocardiography; GDS, Global Deterioration Scale; MMSE, Mini-Mental State Examination; MRI, magnetic resonance imaging; PET, positron emission tomography; S-IADL, Seoul-Instrumental Activities of Daily Living; TC, telephone consultation; V, visit; VOSP, visual object and space perception battery

During the screening visit, blood samples (for analyses of thyroid function, folic acid, and vitamin b12; syphilis screening; and apolipoprotein E genotyping), echocardiography (ECG), neuropsychological test battery, brain MRI, and amyloid PET will be collected. These results are needed to screen for other causes of cognitive impairment and to only recruit patients with MCI in the Alzheimer’s continuum.

Allocation will occur after baseline screening. Donepezil will be packed with clear dosing instructions and schedule. At visit 1, detailed baseline assessments will be required of all participants. Then, participants allocated to the donepezil group will be instructed to consume a dose of 5 mg once daily for the first 4 weeks. The participants allocated to the control group will not be administered donepezil during the study period. At visit 2, follow-up assessments of the measures of efficacy, except for VOSP, and detailed reporting of potential adverse effects will be required of all participants. Participants allocated to the donepezil group will then be instructed to increase the dose to 10 mg once daily for the next 8 weeks. At visit 3, follow-up assessments, including all measures of efficacy performed at baseline, and detailed reporting of potential adverse effects will be required of all participants.

V1, V2, and V3 measurements will be acquired with the following means.1. Eye-tracking metrics during the simplified RCFT and CDT on a digital tablet.2. MMSE3. CDR4. GDS5. S-IADL6. VOSP (VOSP is not performed at V2).7. Digital pen data during simplified RCFT copying test on digital tablet [13]

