## Data collection and management

### Plans for assessment and collection of outcomes {18a}

All research staff will be trained in the acquisition of eye-tracking metrics and digital pen data. The MMSE, CDR, GDS, S-IADL, and VOSP will be performed by authorized clinical psychologists. The assessments will be performed based on the study schedule.

Eye-tracking will be recorded during the copying of the simplified RCFT. After standard gaze mapping, we will quantify eye-tracking metrics such as the number and duration of fixations, saccades, and switching between perception and working areas. These quantified metrics will be compared between the donepezil and control groups.

The digital pen trajectory will be recorded during the copying of the simplified RCFT. After preprocessing, we will quantify digital pen data, such as pen stroke, drawing boundary, and drawing area. These quantified metrics will be compared between the donepezil and control groups.

If the parametric test requirement is not satisfied with the missing data, a non-parametric test will be used.

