### Data management {19}

To promote data quality, participants’ trial data, including cognitive tests, laboratory tests, and medical history, will be summarized in the CRF. These paper CRFs will be stored in the individual participant’s folder. The participants’ data will be kept anonymous in all trial-specific documents, except for signed consent. Each participant’s eye-tracking data and digital pen data will be stored in a trial folder in the electronic database. Participants will be identified only by an identification number on the CRF and any electronic database. All documents will be stored safely under confidential conditions. Data entry will also be supervised by the PI to ensure that there are no transcription errors.

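### All staff are left unblinded, raters and data processors included, and the one safeguard, an eye-tracking primary outcome, does not protect the secondary ratings

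*Protocol article*

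**What the plan says.** Three sections of the protocol article cover blinding. Concealment mechanism {16b} says that "participants, caregivers, principal investigator, and all staff will not be blinded after allocation". Who will be blinded {17a} repeats that "participants, caregivers, principal investigator, and staff will not be blinded", and Procedure for unblinding {17b} says the same of all research staff. None of them sets raters or data processors apart.

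One mitigation is offered, in Sequence generation {16a}: "To minimize bias in the open-label study, we will set the primary outcome as eye-tracking metrics rather than clinical rating scores".

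Plans for assessment and collection of outcomes {18a} describes how outcomes are produced:
- Rating scales: "The MMSE, CDR, GDS, S-IADL, and VOSP will be performed by authorized clinical psychologists".
- Eye-tracking: "After standard gaze mapping, we will quantify eye-tracking metrics such as the number and duration of fixations".
- Pen data: "After preprocessing, we will quantify digital pen data, such as pen stroke, drawing boundary, and drawing area".

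There is no placebo. Under Intervention description {11a}: "The participants allocated to the control group will not be administered donepezil during the study period". Data management {19} adds: "Participants will be identified only by an identification number on the CRF and any electronic database".

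**The concern.** Open treatment is disclosed and is not the point. The point is that assessment and processing are left open too, although they can be masked separately from treatment.

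By choosing eye-tracking over clinical rating scores in order to limit bias, the sponsor accepts that rating scores are vulnerable when the arm is known. Those scores nevertheless remain as secondary measures, with no protection. They also serve as comparators. The abstract says the trial is to show whether eye-tracking detects an effect more sensitively, and Methods for additional analyses {20b} plans to correlate eye-tracking metrics with cognitive test scores. A rating shifted by knowledge of the arm would affect both its own between-group comparison and those comparisons.

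For the primary endpoint, an instrumented measurement removes rater opinion at the moment of recording. It does not by itself remove discretion afterwards, if gaze mapping leaves any.

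**Working it through.** **1. Which outcomes the safeguard covers**

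| Outcome | Produced by | Role for judgement or informant report | Covered by the {16a} safeguard? |
|---|---|---|---|
| Fixation-count ratio (primary) | Recording, then gaze mapping and quantification by the study team | Depends on how automatic the mapping is; not stated | In part |
| Pen data | Recording, then preprocessing and quantification by the study team | Not stated | Not mentioned |
| CDR, GDS, S-IADL | Clinical psychologists | Highest | No |
| MMSE, VOSP | Clinical psychologists | Lower, but scored by a person who may know the arm | No |

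The legend to Fig. 3 defines the two areas for the figure-copying task as the upper and lower halves of the display. Assigning a fixation to an area is therefore geometric once the gaze is mapped. What remains open is the mapping step itself.

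**2. Whether the identification number already masks the files**

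Implementation {16c} gives identification numbers in sequence and allocates according to that sequence. Anyone with the allocation list can read the arm from the number. The coding described in Data management {19} protects confidentiality but does not mask the arm.

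**3. The plan's own sample size**

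Inputs from Sample size {14}: standardized effect 0.8, two-sided alpha 0.05, two-sample t-test, 90% power, 12% attrition. With n per group, df = 2n − 2 and noncentrality λ = δ√(n/2):
- n = 33: power 89.3%.
- n = 34: λ = 0.8 × √17 = 3.30, power 90.2%.
- 34 / 0.88 = 38.6, rounded up to 39 per group, 78 in total.

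The stated figures reproduce, and masking assessment changes none of them.

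**4. Illustration of scale**

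The article gives no bias size, so the shifts below are assumptions. Suppose the drug has no effect on an outcome and knowledge of the arm moves the between-group difference by δ SD. The rejection probability of the nominal 5% test at 34 per group (df = 66) is P(T > t₀.₉₇₅) + P(T < −t₀.₉₇₅), where T is noncentral t with λ = δ√17:

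| Assumed shift δ | λ | Rejection rate |
|---|---|---|
| 0.1 | 0.41 | 6.9% |
| 0.2 | 0.82 | 12.8% |
| 0.3 | 1.24 | 23.0% |
| 0.4 | 1.65 | 36.9% |

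With all 39 per group analysed, the rates at 0.2 and 0.3 become 14.1% and 25.8%. The figures apply to one outcome at a time and to the t-test. Ordinal outcomes go to the Mann–Whitney test, for which they are only a guide.

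**The case against.** The best case for the plan is that it is openly unblinded, gives a reasoned mitigation and chooses a primary endpoint that no one rates by eye. Mapping is called standard and the areas of interest are fixed. An article need not spell out the processing workflow, and the full protocol is not shown. Much of this stands, and it limits what can be said about the primary endpoint.

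A reader might go further than the document allows in several ways:
- **Case-by-case coding of the primary endpoint by unblinded staff.** Not supported. The areas are fixed, preprocessing is mentioned only for pen data, exclusion of recordings is not described, and neither the operator nor the degree of automation is given.
- **Bias in favour of donepezil on the fixation ratio.** The article states no favourable direction for the ratio.
- **Rating bias that undermines both study hypotheses.** Too strong. The first hypothesis is tested primarily by eye-tracking, and of the rated scales only the VOSP bears on visuospatial function. The second names no rating scale as its benchmark. Ratings shifted towards donepezil would make the conventional scales look more sensitive, which works against the eye-tracking claim.
- **Raters already separate from the enrolling team.** The article names the roles but does not say that they are different people.

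What the objection does not answer is that the article states, rather than merely omits, that all staff are unblinded, and that its mitigation does not reach the rated outcomes.

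**Conclusion.** The point holds in limited form. For the MMSE, CDR, GDS, S-IADL and VOSP the plan has no protection against knowledge of the arm, and the comparator is untreated. For the primary endpoint, protection extends only as far as gaze mapping is automatic. If it is fully automatic, the risk at that step is small and the gap in the secondary ratings remains.

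The size of the bias is not estimable from the document. The 12.8% and 23.0% rest on assumed shifts of 0.2 and 0.3 SD with 34 evaluable per arm. They are not the trial's error rate, and a shift in a rating cannot move the eye-tracking endpoint. That masking is feasible is an inference from the named rating role and the coded files; the article does not discuss it. This is a worthwhile, inexpensive improvement, not a flaw that invalidates the primary analysis.

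**What to change.** Keep treatment open. Amend Concealment mechanism {16b}, Who will be blinded {17a} and Plans for assessment and collection of outcomes {18a}, and bring {17b} into line:

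1. **Recordings.** Carry out gaze mapping, eye-tracking quantification and pen-data preprocessing on files that bear a random code for participant and visit in place of the sequential study number. Lock the results before they are linked to arm. This works even if the people processing the files know individual allocations. State how far gaze mapping is automatic.
2. **Ratings.** Do not tell the arm to the clinical psychologists who already rate. Have someone else collect adverse-event and dosing information, since adverse effects are reported at the same visits as the ratings. Ask participants and caregivers not to disclose the arm to the rater, and log any unmasking.

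The trial is ongoing. The first change can also be applied to stored recordings not yet processed; the second can apply only to visits still to come.

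The cost is a recoding step, some care in organising visits and occasional accidental unmasking. No additional participants are needed: 34 evaluable per group and 78 enrolled stand. Participants' own expectations and caregivers' knowledge of treatment would still influence results, and the report should say so.
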